## Abstract

**Background:**

The identification of the attribution of economic value that users of a health system assign to a health service could be useful in planning these services. The method of contingent valuation can provide information about the user's perception of value in monetary terms, and therefore comparable between services of a very different nature. This study attempts to extract the economic value that the subject, user of primary care nursing services in a public health system, attributes to this service by the method of contingent valuation, based on the perspectives of Willingness to Pay (WTP) and Willingness to Accept [Compensation] (WTA).

**Methods/Design:**

This is an economic study with a transversal design. The contingent valuation method will be used to estimate the user's willingness to pay (WTP) for the care received from the primary care nurse and the willingness to accept [compensation] (WTA), were this service eliminated. A survey that meets the requisites of the contingent valuation method will be constructed and pilot-tested. Subsequently, 600 interviews will be performed with subjects chosen by systematic randomized sampling from among those who visit nursing at twenty health centers with different socioeconomic characteristics in the Community of Madrid. The characteristics of the subject and of the care received that can explain the variations in WTP, WTA and in the WTP/WTA ratio expressed will be studied. A theoretical validation of contingent valuation will be performed constructing two explanatory multivariate mixed models in which the dependent variable will be WTP, and the WTP/WTA relationship, respectively.

**Discussion:**

The identification of the attribution of economic value to a health service that does not have a direct price at the time of use, such as a visit to primary care nursing, and the definition of a profile of "loss aversion" in reference to the service evaluated, can be relevant elements in planning, enabling incorporating patient preferences to health policy decision-making.

## Background

The definition of health policies has an ethical dimension that is not faithfully reflected in the rest of planning, and which is probably provided by the conception of health as a fundamental good for human beings [1]. The main challenge of these policies is to approach the health needs of the population as effectively and efficiently as possible. A key element in the definition of health policies is the availability of resources and their distribution among the different services that provide them.

In our setting, the health system if organized as a national system and provides its services through an organization at two levels, so-called Specialized Care (SP), and Primary Care (PC). Although for nearly 30 years primary care has been defined as the entry-door structure to the system and the management of the health needs of patients, in recent years this care level has undergone a significant process of "disinvestment" [2]. Valuation of the public health system, its needs, its effectiveness and efficiency and its role in the social structure is a highly complicated task. But this tendency to reduce investment in primary care is not justified by an analysis of the social needs expressed by health demand, because demand for primary care is high, and increasingly so among those with a poorer perception of their state of health [3]. Nor is it supported by the study of people's preferences, or by the results of the impact on health at each care level in the population as a whole, because as far as it is known, investment in primary care is accompanied by more efficient health results [4].

In the context of reducing investment, a study of the perception of value perceived by users of primary care services appears timely. There is no way to determine this perception of value when the service evaluated is not provided under market conditions and cannot be identified by a price tag. This is why the contingent valuation method is used to answer these questions. The contingent valuation method attempts to simulate a hypothetical market by surveying consumers. The objective of the interview is to create a hypothetical scenario in which the subjects interviewed represent demand and the interviewer plays the role of supply. The contingent valuation method is based on theoretical economics and assumes that individual preferences can be interpreted in the form of a function of utility, where two different states (initial and final) can be compared in terms of the changes in the utility function. Willingness to Pay (WTP) and Willingness to Accept [Compensation] (WTA) are the measures proposed in the framework of welfare theory, which attempt to value, in monetary terms, gains and losses in utility an individual experiences when a project or intervention is introduced or eliminated. Initially, this method was utilized to value public goods not subject to the market, but today its use has been extended to value quasi-public goods, such as those provided by health services. The contingent valuation method is especially suitable in the case of the valuation of health care because it includes use values and non-use values, that is, the value derived from the consideration of the product as a consumer good and those related to the existence of the service itself [5]. The contingent valuation method has been employed in the field of primary care to estimate the willingness to a defray improvements in health care in systems under development [6], to evaluate health promotion programs [7], mental health care [8], the extension of certain health coverage [9], and the willingness to pay for informal care [10]

The perception of value of the service can be studied as a whole or in its components. The Basic Care Unit (BCU), also called the Family Care Unit (FCU), constitutes the basic care pillar of primary care, and is composed of a family physician and a family or communitary nurse. In a previous study we evaluated the perception of economic value the user expressed of the visit to the family physician. This made clear that not setting a direct payment at the moment use of the service, that is, the absence of a price tag, did not represent the absence of the perception of value [11]. But no information is available about the perception of value the user has of primary care nursing services. Knowing the monetary value that users of a health system assign to a certain service could be useful in deciding the level of investment and "amount of need" to which a response must be given, this constituting an unmistakable expression of the user's own preferences.

The value attributed to a good or service by contingent valuation methodology can be studied from the perspective of willingness to pay (WTP) for the enjoyment of the good, or by willingness to accept [compensation] (WTA) for its removal. Being valuations of the same good, the two approaches should produce similar values. However, we know that values obtained by WTA are consistently higher than those expressed by WTP, when valuing the same good [12,13].

There are several theories to explain these differences between WTP and WTA. Attempts have been made to explain this by economic theory; this is because certain goods cannot be easily substituted (the utility they provide cannot be easily replaced by another consumption), which requires greater compensation for its loss [14]. But perhaps the most studied idea is "loss aversion." An experimental situation has been described, known as the "endowment effect," according to which, subjects who have been provided with a good and are asked how much money they would have to be paid to give it up, ask for amounts that far exceed the amounts offered by similar subjects who have not had the opportunity to buy the good. This theory emphasizes resistance to loss as an explanation of the difference between WTP and WTA. Loss aversion can be understood assuming that the marginal utility of the individual decreases. That is, an improvement in health produces a change in utility lower in absolute value, a lower marginal utility, than a loss of health in the same degree [15]. This leads us to think that, knowing the differences between WTP and WTA for a good or service, can help us understand not only the value, but also the possible resistance to "loosing" a good or service. This is why the valuation of certain health services from the perspectives of WTP and WTA can be a useful tool in health planning.

In summary, we find ourselves in a setting of providing public health services, the user of which is not used to valuating in terms that enable comparing them with other goods or services. The planner puts a price on this good by references, some objective (health results), others subjective (satisfaction), useful, but not valid when making these kinds of comparisons. Contingent valuation methodology can provide us with information about the user's perception of value in monetary terms and, therefore, comparable between services of a very different nature. Additionally, this methodology enables us to evaluate to a certain degree adherence to the service by evaluation of "resistance to loss", specifically, in the evaluation of the service provided by the nurse in primary care. Knowing these two circumstances, perception of economic value and resistance to loss, would be most valuable in planning health provisions and interpreting the preferences of the people to which this service is addressed.

## Methods/Design

### Design

This is an economic study with a transversal design. The contingent valuation method will be used to estimate willingness to pay (WTP)/willingness to accept [compensation] (WTA), for health care received in a primary care nursing visit in a public health system in the Community of Madrid. This is done by personal interviews of the users of these services.

### Subjects of study

Included are persons older than 18 years of age who use the primary care nursing service. To be included they must have experience in the exchange of goods in market conditions, to be able to understand the scenarios posed, understand Spanish correctly, and consent to be interviewed.

Criteria for exclusion are not understanding the language, being unable to give their consent or not understanding the objective of the interview.

### Sample size and obtaining the sample

If we wish to estimate the parameter (WTP or WTA) with sufficient precision so that the confidence interval will have an amplitude of less than 15% of the standard deviation (30% precision), for a confidence of 95%, and with the common formulas for this calculation, we will need to include 170 subjects. However, we will be studying groups of subjects (health centers) in which the variability of the parameter being studied will be less among the subjects of the group and greater among the subjects of the different groups. This is the definition of the "design effect," which causes estimates to lose efficiency compared with purely random sample selection systems. Measuring the size of the design effect depends on the relationship between the intragroup and intergroup variances, specifically what is called the Intraclass Correlation Coefficient (ICC), and the number of subjects studied in each group. In a previous paper that evaluated the WTP for a medical visit, the value of the ICC was 0.048. Estimating an unfavorable scenario in which the ICC was 50% greater (ICC approx. 0.075), and including an approximate number of 30 patients/center, the design effect would be equal to 3.18, which would bring us to include 543 subjects (170 × 3.18). Since there has to be a percentage of incomplete interviews, or patients who fail to reveal the necessary information for subsequent analyses, and given that the marginal cost of each new interview is small, and is not an inconvenience for the subject interviewed, our inclusion objective will be 600 patients. This represents the recruitment of about thirty patients at twenty health centers.

#### Sampling

The study sample will be selected by systematic randomized sampling carried out at health center nursing visits, after first requesting their consent to participate. The health centers are stratified based on two characteristics, rural or urban populations and average income of the district in which they are located. Health centers will be selected from the upper income tercile and lower income tercile, based on data published in the last report available from the National Statistics Institute for the Community of Madrid. This will ensure the inclusion of patients from health centers equally distributed from the two ends of the income distribution terciles, and at least one in five with rural characteristics.

At each health center, on the date of the study, a number of patients will be selected by systematic randomized sampling from an anonymous randomized list of patients with nursing visit appointments, until the number fixed for that is center is reached.

### Measuring tools and variables included

The contingent valuation method requires individual interviews to estimate WTP and WTA. The interview will be performed by skilled personnel, trained in the methodology of the study and who are from outside the health system. The place of the interview will be the health center itself, but outside the care area (library, meeting room, etc.). In case of house calls, patients will be previously contacted by their nurse who will obtain their informed written consent, and the interview will be over the telephone.

A survey that can be filled out in approximately twenty minutes will be handed out at the interview.

First of all, the adaptation and pilot test of the survey will be performed. The quality of the information collected depends in large measure on having an information collecting tool that will clarify for the persons studied the following aspects: objective of the study, product attributes, context of the exchange to be valued, range and certainty of payment and social context. The survey will have a first section that will explain the objective of the study as the economic value of the nursing visit, and certain attributes will be defined such as the universality of care, accessibility and, broadly speaking, the services portfolio. The second section will be the economic valuation itself. Two scenarios will be presented here: the first makes explicit the WTP for the service in question. The second will ask about WTA, if this service were to be eliminated. The monetary measure of the variation in the utility communicated will refer to a compensatory variation framework (compensation required so that, following the exchange, the utility remains) of the classification proposed by O'Brien and Gafni [16]. The payment format will be a direct payment. The type of question will be in a rank format or "payment card," as this format causes the user to behave as if he or she would be in a setting in which the same product was being sold at different prices [17]. The questions will be posed in two parts, the first presenting only three options that include the terciles of the values obtained in the pilot test, and a second payment card that reduces the response given to at least five values equidistant for each tercile; this limits any possible bias for inducing a response.

The cutoff points will be decided by consensus of the research team following the pilot test. The questions in the pilot test on WTP and WTA will be made in an open format. In the questionnaire, the payment cards will include the value 0, and subsequently there will be a question that differentiates so-called "protest zeros" (do not accept the question itself), from the inability to make the payment.

The third and final section of the survey will collect, at least, the following characteristics, which will be transformed into independent variables in the study:

- Characteristics of the center: Rural/urban; Average income of the area

- Sociodemographic characteristics:

- Age in years.

- Sex: male/female

- Employment situation: active worker/unemployed or student/pensioner not retired/retired

- Education level attained: no education/primary/secondary/university

- Social class: (Categories I, from highly specialized professions to V, least specialized).

- Income level: sum of total weighted family income (Total/N^0.5^)

- Characteristics of use of service:

- Frequency: Number of nursing visits in last year

- Type of visit (depending on place of care): health center/domicile

- Type of visit (depending on type of service): promotion and prevention activities; care/monitoring pathologies/chronic processes; identification/monitoring of care plans; diagnostics and therapeutics procedures.

- Need of use of the service:

- Number of chronic pathologies suffered (requiring care for more than six months)

- Hospital admissions in last year (yes/no)

- Health-Related Quality of Life (HRQL) measured by EuroQol 5D

- Type of living arrangements: alone/with partner only/family nucleus/extended family nucleus. Family APGAR

- Caregiver of another person due to illness or incapacity. Yes/no

- Satisfaction with service: AMABLE questionnaire

### Analysis of the data

The value provided by WTP and WTA will be selected for the descriptive analysis and these will be treated as continuous variables, which will be defined by their measures of central tendency and dispersion.

Continuous independent variables will be defined by the same parameters, and discrete variables by an estimate of the proportions and their confidence intervals of 95%. For an estimate of the confidence intervals the variance inflation factor caused by the type of sampling in conglomerates will be taken into account. Consistency of WTP and WTA will be evaluated in a subgroup of subjects by the intraclass correlation coefficient (ICC). To calculate the consistency of the response, the WTP and WTA question will be repeated by telephone to 100 randomly selected subjects, which enables estimating an ICC of around 0.9 with a minimum precision of 7.5%, with a confidence of 95% [18]. Evaluation of the consistency of the response, though this will depend considerably on interpersonal variability, will serve to evaluate the internal validity of the result [19]. The relationship between WTP and WTA will be measured by Pearson's correlation coefficient or Spearman's rho, as well as the ICC.

Univariate analysis will be performed to study the association of the independent variables with WTP, employing parametric tests for continuous variables that are distributed according to a normal distribution and non-parametric tests for the rest.

To validate the model and study the WTP/WTA relationship, two multilevel mixed linear models will be constructed. The variables referring to the individual will constitute the first level, and contextual variables (referring to the clusters or health centers) will make up the second level [20]. The model will be explanatory, given the design of the study. In case the contextual variables do not explain a significant part of the variance we will resort to classical multilevel models with robust estimators of the regression coefficients (Eicker-White estimator) that minimize the problems of heteroscedasticity [21]. The dependent variable of the models will be WTP or the WTP/WTA ratio, net or softened in its logarithmic expression. The independent variables will be introduced depending on their explanatory role in the model, and the final model will be chosen by the principles of maximum parsimony.

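### The univariate tests of association with WTP are chosen by normality alone, with no stated provision for clustering by health centre; unadjusted, the two centre-level variables would have about 20-27% type I error

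*Protocol article*

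**What the plan says.** All references are to the protocol article.

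- **Analysis of the data, univariate step.** The association of the independent variables with WTP is to be studied by "employing parametric tests for continuous variables that are distributed according to a normal distribution and non-parametric tests for the rest". No other criterion is given for choosing the test, and no significance level is stated.
- **Analysis of the data, descriptive step.** Here clustering is provided for: "For an estimate of the confidence intervals the variance inflation factor caused by the type of sampling in conglomerates will be taken into account".
- **Analysis of the data, models.** Two multilevel mixed linear models follow, with individual variables at the first level and health-centre variables at the second.
- **Sample size and obtaining the sample.** The study is sized for clustering. "In a previous paper that evaluated the WTP for a medical visit, the value of the ICC was 0.048"; under an ICC of about 0.075 and roughly 30 patients per centre, "the design effect would be equal to 3.18". The target is 600: "This represents the recruitment of about thirty patients at twenty health centers".
- **Measuring tools and variables included.** The list of independent variables has two that describe the centre, not the patient: rural/urban and average income of the area. The Sampling section stratifies centres on these same two characteristics.

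**The concern.** Read in the ordinary way, a choice between parametric and non-parametric tests by normality means a t-test, ANOVA or correlation, or the rank equivalents. All of these assume independent subjects. The study takes about 30 patients from each of 20 centres and expects their WTP values to be correlated within centre.

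The consequence is largest for a variable that is constant within a centre, because the comparison then rests on 20 centres and not on 600 people. Rural/urban and area income are such variables. The Discussion says the valuation is complete only once WTP is related to needs, satisfaction and socioeconomic situation. A spurious univariate association with area income could therefore be read as support for the validity of the method.

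**Working it through.** **Inputs from the article:** 20 centres, about 30 subjects each; ICC of WTP 0.048 (medical-visit study) and about 0.075 (unfavourable scenario); 95% confidence; 170 subjects before clustering; design effect 3.18; 543 after clustering. **Assumed:** two-sided test at 5%, and no true association.

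**1. The article's own figures.**

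- Unclustered size, reading 15% of the SD as the half-width: (1.96 / 0.15)² = 170.7, against 170 stated.
- Design effect: 1 + (30 − 1) × 0.075 = 3.175, against 3.18 stated.
- Clustered size: 170 × 3.18 = 540.6, or 171 × 3.175 = 542.9, against 543 stated.

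These agree within rounding. (A 50% increase on 0.048 is exactly 0.072; the article rounds up to 0.075.)

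**2. Unadjusted test of a centre-level variable.** The true variance of the estimated difference is larger than the test assumes by the design effect DE = 1 + 29 × ICC. The actual type I error is therefore 2 × [1 − Φ(1.96 / √DE)].

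| ICC of WTP | DE | 1.96/√DE | Type I error | Effective size, 600/DE |
|---|---|---|---|---|
| 0.048 | 2.392 | 1.267 | 20.5% | 251 |
| 0.072 | 3.088 | 1.115 | 26.5% | 194 |
| 0.075 | 3.175 | 1.100 | 27.1% | 189 |

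**3. Check by simulation.** Null data were generated with 20 centres of 30 and normal errors, with centres split 10:10 (as for the two income terciles) and 4:16 (one in five rural). There were 20,000 runs for the t-tests and 4,000 for Mann-Whitney. Ranges are over the two splits.

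| ICC of WTP | t-test on 600 | Mann-Whitney on 600 | t-test on 20 centre means |
|---|---|---|---|
| 0.048 | 20.3-20.6% | 19.1-19.7% | 4.9-5.1% |
| 0.072 | 26.2-26.3% | 24.8-25.7% | 5.0% |
| 0.075 | 27.5-27.7% | 26.1-26.7% | 5.0-5.1% |

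Switching to a rank test does not help, because the fault is dependence and not shape. Working on centre means restores the nominal level.

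**4. Individual-level variables.** Here DE is approximately 1 + 29 × ICC_x × ICC_y, where ICC_x is the covariate's own clustering. The article gives no ICC_x, so a range of 0.01 to 0.30 is assumed.

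- WTP ICC 0.048: DE from 1.014 to 1.418, type I error 5.2% to 10.0%.
- WTP ICC 0.075: DE from 1.022 to 1.652, type I error 5.3% to 12.7%.

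The upper end would apply to variables that differ strongly between centres, as income or social class might; the lower end to those that hardly differ.

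**The case against.** The strongest reply has three parts.

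*The defect is inferred from silence.* The article names no specific test and excludes no adjustment. It condenses a fuller protocol, and its authors plainly understand clustering. This stands in part: a reader might infer that the plan declares the 600 subjects independent, and it does not. But the article does more than leave the matter open. It states a rule for choosing the tests, the rule turns on normality alone, and the steps on either side both provide for clustering. Followed as written, it leads to ordinary tests.

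*The explanatory inference rests on the multilevel models.* These place centre variables at the second level. Covariates enter for what they explain and parsimony settles the final model; the univariate p-values are not said to be an entry filter. This stands. A reader might infer that false univariate associations will pass into the study's conclusions, but the text does not support that. The univariate analysis nevertheless remains a separate planned analysis, and its error rates should be right.

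*The inflation is confined.* The full effect falls on 2 of about 18 listed variables. This also stands, and a claim that every characteristic is tested at 20% or more would be wrong.

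A reader might further expect the cluster-adjusted intervals to contradict the unadjusted p-values. The interval sentence belongs to the descriptive analysis, and no interval for a univariate comparison is announced, so the article sets up no such pair.

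**Conclusion.** The concern holds in a limited form. The stated test rule makes no provision for clustering. If it is applied to individual subjects, type I error is about 20% at ICC 0.048 and 27% at ICC 0.075 for rural/urban and area income, and about 5-13% for individual-level variables.

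These figures depend on a two-sided 5% level, which the article does not give; on 30 subjects per centre; on an ICC taken from medical visits holding for nursing visits; and, for individual-level variables, on the assumed covariate ICCs. Because the multilevel models limit the effect on the final explanatory conclusions, this should be fixed but need not hold up the study.

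**What to change.** Add one sentence to the univariate paragraph saying that these associations will account for health centre. Either of two routes would do:

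- one-covariate linear mixed models with a random intercept for centre and small-sample degrees of freedom, using a transformation that allows zeros if WTP is skewed (the payment cards include 0, so a plain logarithm would fail); or
- for the two centre-level variables, tests on the 20 centre means.

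The cost is a little extra analysis within the mixed-model framework already planned, and larger p-values. The increase should generally be slight for individual-level variables and more noticeable for rural/urban and area income, where 600 subjects carry the information of only about 189 to 251 independent ones. No change to sampling or data collection is needed.
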